# Enhancing Pragmatic Language skills for Young children with Social communication difficulties (E-PLAYS-2) trial: study protocol for a cluster-randomised controlled trial evaluating a computerised intervention to promote communicative development and collaborative skills in young children

**DOI:** 10.1186/s40359-024-01749-y

**Published:** 2024-05-13

**Keywords:** Social communication, Pragmatic language, Randomised controlled trial, Feasibility study, Young children, Peer collaboration, Communication impairment, Computer game

## Abstract

**Background:**

A number of children experience difficulties with social communication and this has long-term deleterious effects on their mental health, social development and education. The E-PLAYS-2 study will test an intervention (‘E-PLAYS’) aimed at supporting such children. E-PLAYS uses a dyadic computer game to develop collaborative and communication skills. Preliminary studies by the authors show that E-PLAYS can produce improvements in children with social communication difficulties on communication test scores and observed collaborative behaviours. The study described here is a definitive trial to test the effectiveness and cost-effectiveness of E-PLAYS delivered by teaching assistants in schools.

**Methods:**

The aim of the E-PLAYS-2 trial is to establish the effectiveness and cost-effectiveness of care as usual plus the E-PLAYS programme, delivered in primary schools, compared to care as usual. Cluster-randomisation will take place at school level to avoid contamination. The E-PLAYS intervention will be delivered by schools’ teaching assistants. Teachers will select suitable children (ages 5–7 years old) from their schools using guidelines provided by the research team. Assessments will include blinded language measures and observations (conducted by the research team), non-blinded teacher-reported measures of peer relations and classroom behaviour and parent-reported use of resources and quality of life. A process evaluation will also include interviews with parents, children and teaching assistants, observations of intervention delivery and a survey of care as usual.

The primary analysis will compare pragmatic language scores for children who received the E-PLAYS intervention versus those who did not at 40 weeks post-randomisation. Secondary analyses will assess cost-effectiveness and a mixed methods process evaluation will provide richer data on the delivery of E-PLAYS.

**Discussion:**

The aim of this study is to undertake a final, definitive test of the effectiveness of E-PLAYS when delivered by teaching assistants within schools. The use of technology in game form is a novel approach in an area where there are currently few available interventions. Should E-PLAYS prove to be effective at the end of this trial, we believe it is likely to be welcomed by schools, parents and children.

**Trial registration:**

ISRCTN 17561417, registration date 19th December 2022.

Protocol version: v1.1 19th June 2023.

## Background

Children who have difficulties with social communication (also known as pragmatic language ability) experience problems with using language for social purposes. Whilst their knowledge of grammar and vocabulary may be adequate or even advanced, they struggle with communicative tasks such as appropriate use of greetings, conversational turn-taking, understanding non-literal language such as jokes, irony or sarcasm, social conventions such as politeness, taking the perspective of their listener and responding with relevant information [1].

'Social communication difficulties' (SCDs) or 'pragmatic language impairments' represent a continuously distributed trait in the population. This trait includes individuals at the extreme end who are diagnosed with autistic spectrum disorder and/or severe language disorders but also a much larger group who show milder, but still detrimental, communication difficulties [2].

Children with SCDs are commonly rejected and victimised by peers [3, 4] and can be severely disruptive [5–7]. In groups, they fail to contribute appropriately, and are often ignored or dominated by peers [8, 9]. Children with pragmatic language problems experience lower quality of life; in adulthood these individuals experience more mental health problems, lower academic achievement and make fewer friends [10]. Health economic evaluations have also been called for as healthcare costs have been shown to be 36% higher for children with language disorders at 4–5 years old [11].

These communication difficulties frequently cause troubled interactions with family, peers, teachers and the criminal justice system [12, 13]. For primary school children of low socio-economic status, pragmatic language skills appear to be especially important [14].

Children with language difficulties in the UK are served by NHS Speech and Language therapists and/or by schools’ own speech and language services and schools’ other provisions. However, services are stretched, particularly since the pandemic. Furthermore, schools and speech and language therapists have few rigorously tested interventions that they can use for SCDs. The most recently available surveys of usual care reported a ‘proliferation of locally-developed programmes based on clinical experience’ due to a lack of ‘strongly evidence-based programmes’ [15, 16]. These findings were borne out by interviews with schools and speech and language therapists in our earlier work [17]. Activities typically include exercises on turn-taking, topic management, and conversational skills, sometimes with role-play or modelling. There is little evidence concerning the efficacy of these constituent activities [16]. Whilst the use of technology and gaming has been highlighted as a positive tool for facilitating communication and collaboration in children with social communication difficulties [18, 19], its use is generally viewed as emerging rather than established [20].

E-PLAYS (Enhancing Pragmatic Language skills for Young children with Social communication difficulties) is a computer-based intervention that has been developed and piloted by our team.

Collaborative and team-building skills are recognised as vital to future adult employment and participation in society [21]. However, some of the most challenging contexts for children with social communication difficulties are precisely those requiring collaboration, such as joint problem-solving or creative free play [8, 9, 22, 23]. E-PLAYS aims to facilitate and enhance children’s interactions by providing socio-cognitive scaffolding within a fun, cooperative computer game.

E-PLAYS supports communication based around naturalistic play with a peer and aims to embed learning in relevant contexts, thus promoting the generalisation of these social skills.

An earlier version of E-PLAYS (known as the Maze Game [9, 23]) was tested on 32 children. Children receiving the intervention showed significant improvement by comparison to a control group on pragmatic language test scores. A recent feasibility study of E-PLAYS [17] with 50 children showed good response and completion rates, realistic recruitment and high acceptability by children and schools. These studies laid the groundwork for the present study which will conduct a randomised controlled trial of E-PLAYS seeking to establish its clinical- and cost-effectiveness.

## Design and methods

### Aim

The aim of the E-PLAYS-2 trial is to establish the effectiveness and cost-effectiveness of care as usual plus the E-PLAYS programme, which is designed to improve pragmatic language skills in children with social communication difficulties, delivered in primary schools, compared to care as usual.

### Trial design

The E-PLAYS-2 trial is a multi-centre, two-arm, cluster-randomised controlled trial with an internal pilot.

### Setting

The trial will take place in state-funded mainstream primary schools and state-funded special primary schools in Bedfordshire, Hertfordshire and North London. Following slightly lower than anticipated recruitment during the internal pilot phase, primary schools in Buckinghamshire will also be recruited for the main trial.

### Participants

Both the school and the children’s parents/carers must agree to take part before either may be included. Eligibility to take part will be ascertained using the following criteria.

### School eligibility

#### Inclusion criteria:

A state-funded infant or primary school or special needs school based in the target recruitment areas;

#### Exclusion criteria:

Independent, fee-paying schools;Schools participating in other language and communication research/trials aimed at pupils in Year 1 and Year 2 (aged 5–7 years);Schools who have previously used E-PLAYS;

### Child participants

Teachers will use the Social Communication Behaviour Checklist [24] which comprises a short 5-item questionnaire to confirm or reject their selection for ‘Focal’ children. Similarly, teachers will use the Social Communication Behaviour Checklist to confirm the selected ‘Partner’ children do *not* meet the criteria for social communication difficulties (see ‘Intervention’ section for definitions of Focal and Partner children). Child recruitment will take place prior to school randomisation.

### Child eligibility (Focal children)

Focal child eligibility criteria are as follows:Children aged 5–7 years old;Children who meet the criteria for social communication difficulties as determined by the Social Communication Behaviour Checklist [24];Children whose parents/carers give consent for them to take part in the E-PLAYS-2 trial;Children who have not used E-PLAYS before;Children whose parents/carers are willing to complete relevant questionnaires;Children who complete the key trial baseline assessments (assuming all other eligibility criteria are met);

Baseline and outcome data will be sought for all Focal children (subject to potential withdrawals from some or all aspects of follow-up data collection by participating schools or parents).

### Child eligibility (Partner children)

Partner child eligibility criteria are as follows:Children aged 5–7 years old;Children who do *not* meet the criteria for social communication difficulties as determined by the Social Communication Behaviour Checklist [24];Children whose parent/carers give consent for them to take part in the E-PLAYS-2 trial.

Not all Partner children will complete assessments. We will randomly select one Partner child from each school to complete the Test of Pragmatic Skills (TPS) at baseline and follow-up assessments (see details of the TPS below). This will allow for a comparison of the outcomes in this subsample of typically-developing children between intervention (where the child will partner a participating child in E-PLAYS-2) and control schools (care as usual). Parents/carers of the Partner children will be asked to consent to the Partner child completing the TPS (although only one randomly selected participant in each school will complete these assessments as stated above).

### Intervention

The E-PLAYS programme is designed for children with SCDs aged 5–7 years old (referred to hereafter as ‘Focal’ children). Using a computer game, E-PLAYS guides the Focal child through real-life conversational exchanges with a specific focus on (a) requesting optimally useful information (b) giving helpful directions and (c) asking for clarification. Each Focal child is matched with a ‘Partner’; a typically-developing child from the same year group.

Each E-PLAYS session uses the computer game which is designed for two players using interlinked laptops. There are ten weekly sessions of 30 min each; schools’ teaching assistants are trained to deliver and supervise all sessions. Five sessions are with the Focal child and the teaching assistant only, five are with the Focal and Partner child together supervised by the teaching assistant. Sessions with the classmate (Partner child) give the child an opportunity to practice newly-acquired skills and also to learn collaboration skills through joint problem-solving with a peer. E-PLAYS is web-based, enabling us to distribute E-PLAYS directly to schools. Teaching assistants will self-train using a comprehensive manual with online support. The E-PLAYS software automatically records the number of sessions along with date accessed and sends this data directly to the research team.

### Recruitment

#### School recruitment

Recruitment strategies include directly emailing schools based in the target recruitment areas, use of social media channels and working with contacts in relevant local authorities by providing them with recruitment materials to distribute at a local level. During initial contact, schools will be provided with an information sheet about the trial. Where schools express an interest in participating, a member of the research team will arrange a convenient time discuss the trial with an appropriate staff member (e.g., a Head Teacher or a Special Educational Needs Co-ordinator (SENCO)) in greater detail. Schools wishing to proceed will be required to sign a memorandum of understanding (MoU) agreeing to the expectations of the trial, and a Data Sharing Agreement (DSA) between the school and the research team.

#### School retention and withdrawal

Schools will receive £350 as a thank you for taking part in the trial. This will be paid in instalments by the University of Bedfordshire after key milestones have been reached (such as completion of mid-trial surveys).

Where a school indicates that they wish to withdraw from the study this will result in the full withdrawal of all participants and staff at this school. No further data will be collected. The school will inform the parents/carers that they have withdrawn.

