#### Child consent procedure

All parents will be given the option to speak to a member of the research team or to contact the Chief Investigator in the event of additional questions. Consent to enter the study will be sought from each participant only after a full explanation has been given, an information leaflet offered and time allowed for consideration.

Participation in the study will be entirely voluntary and written informed consent from parents/carers will be obtained before child baseline data is collected and randomisation is conducted. On the consent form, parents/carers will be requested to consent for their child’s school to provide data including child’s name, date of birth, gender, home postcode, ethnicity, religion/belief, English as an additional language (EAL), education, health and care plan (EHCP) status, help received from a Speech & Language Therapist and/or an Educational Psychologist and receipt of Pupil premium and/or free school meals (FSM, a proxy for deprivation) for the purposes of sample description and potentially for use as covariates in analyses. The consent form for Focal children will also request parent/carers to provide their educational qualifications, employment status, ethnicity and consent/commitment to complete the EQ-5D-Y (proxy version 1), CHU-9D, and resource use data questionnaires at specified time-points. Parents/carers will return completed consent forms to the school.

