#### Child and parent/carer retention and withdrawal

At the end of the trial and following completion of all questionnaires, parents/carers of Focal children will receive a £15 voucher to offset any incidental expenses and in recognition of their participation.

All participants are free to withdraw at any time from either the intervention or follow-up data collection without giving reasons and without prejudicing further care. The Chief Investigator will preserve the confidentiality of participants taking part in the study and is registered under the Data Protection Act. If a child does not appear to want to take part at the time the E-PLAYS intervention is being delivered and/or assessments are taking place, their wishes will be respected. Where a parent/carer wishes to withdraw from the study, it will be clarified as to whether they wish their child to withdraw from the intervention or if they themselves wish to withdraw (i.e., stop completing outcome measures). Where withdrawal is only for the participating parent/carer, the child may continue to take part in all other aspects of the trial and follow-up data will continue to be collected when possible. If a Partner child withdraws, another child from the school will be recruited as a replacement for the purposes of intervention delivery.

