### Data management

#### Data collection, management and verification

The five primary sources of quantitative data for this trial are:Data collected by research assistants during school visits at baseline, 15–20 weeks and 35–40 weeks. The TPS and ERRNI will be audio recorded, with these recording being subsequently scored, and the relevant data entered into the REDCap database. All of the other Research Assistant completed measures (CELF-5, Droodles and Communication Test) will be entered into the REDCap database after testing.Data collected from the teachers of participating focal children at baseline, 15–20 weeks and 35–40 weeks (CCC-2 and SDQ). These data will be collected via online Qualtrics surveys sent directly to teachers of participating focal children.Data collected from the parents of participating focal children at baseline, 15–20 weeks and 35–40 weeks. Parent/household demographic data (e.g. parent/carer employment, parent/carer ethnicity etc.) are collected as part of the paper consent forms completed by parents of participating focal children. These forms are returned to the research team who enter these into the REDCap database. Parent completed data for the economic evaluation (i.e. EQ-5D-Y, CHU-9D and resource use) will be collected electronically (via direct entry into the trial REDCap database), or via paper questionnaires (which are subsequently returned to the trial team and entered into the trial database)Data collected directly from the schools of participating children at baseline (provided for both focal and partner children). These data (e.g. age, gender, ethnicity etc.) are entered into password protected spreadsheets by school staff (one for each school). These are then securely shared with the research team.Data collected by research assistants during intervention fidelity assessments.

Monitoring data: E-PLAYS-2 software will record the content, duration and number of intervention sessions each child receives using a unique login ID. Access to the E-PLAYS information is password protected and will be accessed on University computers with Bitlocker Windows security. Data within the E-PLAYS software is anonymised.

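### A school's withdrawal ends all data collection for its children, including parent questionnaires that need no school step, and this conflicts with the partial withdrawal allowed elsewhere in the protocol

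*Protocol article*

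**What the plan says.** The protocol article has four withdrawal provisions that bear on this point.

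- **School retention and withdrawal.** When a school indicates that it wishes to leave the study, "this will result in the full withdrawal of all participants and staff at this school. No further data will be collected". Parents then hear of it from the school.
- **Child eligibility (Focal children).** The aim of gathering baseline and outcome data on every Focal child carries a qualification: "subject to potential withdrawals from some or all aspects of follow-up data collection by participating schools or parents".
- **Child and parent/carer retention and withdrawal.** "All participants are free to withdraw at any time from either the intervention or follow-up data collection". The team clarifies which of the two a parent means. If only the parent is leaving, follow-up of the child continues where possible.
- **Teaching assistant retention and withdrawal.** If an assistant cannot be replaced, affected participants are asked whether they will go on giving outcome data.

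On how data are obtained, the Child consent procedure records the parent's own "consent/commitment to complete the EQ-5D-Y (proxy version 1), CHU-9D, and resource use data questionnaires at specified time-points". Data collection, management and verification says of these parent data that they "will be collected electronically (via direct entry into the trial REDCap database), or via paper questionnaires". Completed paper forms go back to the trial team. The TPS belongs to a different source: "Data collected by research assistants during school visits at baseline, 15–20 weeks and 35–40 weeks".

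**The concern.** The school-level rule is all or nothing, while the neighbouring rules are graded. A staffing problem shows the contrast. If an assistant leaves and cannot be replaced, families are asked whether they will continue in follow-up. If the same problem leads the school to say it wishes to withdraw, nobody is asked and every child is lost.

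Two things are at stake. First, parents who have not withdrawn stop contributing the CHU-9D, which is the primary economic analysis, together with the EQ-5D-Y and costs. Second, outcomes go missing a whole school at a time. The Statistical analysis plan section analyses schools as randomised whatever their engagement, but only among participants with data. Only intervention schools have to run ten weekly sessions, so whole-school loss could be uneven between arms. The revised power figure allows for participant-level attrition and does not mention loss of schools.

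**Working it through.** **1. Which data need the school.** This follows Data collection, management and verification.

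| Data | Route | School needed? |
|---|---|---|
| TPS, CELF-5, ERRNI, Droodles and Communication Test | Research assistant visit to the school | Yes |
| CCC-2, SDQ | Online survey to the teacher | Yes |
| CHU-9D, EQ-5D-Y, resource use | Parent enters into REDCap, or paper returned to the trial team | No school step described |

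The third row is therefore lost through the rule itself. The first two rows can be saved only if a school that stops delivery would still cooperate with follow-up.

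**2. Size of the avoidable parent-data loss.** The revised design has 88 schools with a mean of 4.55 Focal children, so 88 × 4.55 = 400.4 children. Each withdrawing school removes about 4.55 families. Four schools (an assumed number) would remove 4 × 4.55 = 18.2 families. That is 4/88 = 4.5% of the trial, or 4/44 = 9.1% of one arm if all four are in the same arm.

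**3. The plan's own power figure.** Inputs from Sample size calculations (alpha from the original calculation, the rest as carried into the revised one): difference 2, SD 7, pre-post correlation 0.6, ICC 0.05, 4.55 children per school, 20% attrition, 44 schools per arm, two-sided 5%.

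- Adjusted SD = 7 × √(1 − 0.6²) = 5.6
- Analysed children per school = 4.55 × 0.8 = 3.64
- Design effect = 1 + (3.64 − 1) × 0.05 = 1.132
- SE = 5.6 × √[1.132 × (1/(44 × 3.64) + 1/(44 × 3.64))] = 0.666
- Power = Φ(2/0.666 − 1.96) = 85.2%, which agrees with the protocol

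**4. Power with whole schools lost.** The numbers lost are assumed and come on top of the 20% attrition. The SE formula is the same with k₁ and k₂ schools.

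| Schools analysed (intervention/control) | Power |
|---|---|
| 44/44 | 85.2% |
| 40/44 | 83.4% |
| 36/44 | 81.3% |
| 40/40 | 81.7% |

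If instead the whole 20% attrition took the form of lost schools, there would be 44 × 0.8 = 35.2 schools per arm with 4.55 children each. The design effect would be 1 + 3.55 × 0.05 = 1.1775 and power 83.8%.

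**5. Bias.** Suppose a fraction q of intervention schools is lost, and lost and retained schools differ by b points after adjustment. The contrast among those with data then moves by about q × b. With 4 of 44 lost and b = 2, the shift is 0.0909 × 2 = 0.18 points. With 8 of 44 lost it is 0.1818 × 2 = 0.36 points. Both q and b are assumed, and b could have either sign.

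**The case against.** The strongest reply is that the rule covers only schools that wish to leave the study, not schools that fail to deliver E-PLAYS. A reader might infer that the plan drops every non-delivering intervention school, so that the estimate becomes the effect in schools that coped. The documents do not support that. The Principal stratum analyses section expects intervention children with no sessions at all, the Statistical analysis plan section keeps schools in their randomised group regardless of engagement, and the teaching assistant rule keeps families in follow-up when delivery fails. This part of the reply stands.

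It can also be said that a departed school cannot be made to host a TPS visit or fill in teacher questionnaires, so much of the loss would occur under any rule. That stands too, except for a school that would stop delivery but still allow visits. The Participants section makes agreement of both school and parents a condition of entry, and the memorandum of understanding and data sharing agreements are not shown, so it cannot be assumed that parent follow-up may always continue. The fix has to be conditional on that.

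The eligibility wording might be reconciled by treating the school rule as the case of complete withdrawal. But the school rule contains no step to establish which case applies, and the parent rule does.

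Finally, mitigation is planned. The primary model uses the 15–20-week TPS, so schools leaving after that visit still contribute. Sensitivity analyses under different missing-data assumptions are promised for the primary outcome, as is multiple imputation, if appropriate, for the economic data. These soften the loss but do not recover the data.

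**Conclusion.** The point holds as a correctable flaw in the withdrawal rule. The school-level text contradicts the partial school withdrawal foreseen in the eligibility section and departs from the approach taken for parents and teaching assistants. Its clearest cost is parent-reported economic data from families who have not withdrawn, about 4.55 families per school before ordinary non-response. For the TPS, the avoidable part is limited to schools that would stop delivery but still admit assessors.

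A firm claim that the treatment effect will be overstated, or that loss will be heavier in the intervention arm, goes beyond the documents. They give no school withdrawal rates. Control schools, which get no access to E-PLAYS, might also leave. The shift of 0.18 points (9% of the 2-point target) rests on an assumed 4 of 44 intervention schools lost and an assumed 2-point difference. The power cost is modest: 85.2% to about 83.4% for those four schools, and still above 80% with eight lost.

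**What to change.** Reconcile School retention and withdrawal with the Focal child eligibility section and with the parent and teaching assistant rules:

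1. When a school asks to withdraw, record whether it is stopping E-PLAYS delivery, school-based assessments, or both.
2. Ask a school that stops delivery to remain in follow-up, with the 35–40-week TPS visit as the minimum request.
3. After full school withdrawal, continue the CHU-9D, EQ-5D-Y and resource-use questionnaires for parents who have not themselves withdrawn, where the consent form and data sharing agreements allow.

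The cost is wording in the protocol, the memorandum of understanding and the withdrawal form, plus some extra contact with schools and parents. A school keeps its right to refuse further involvement.
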